## Abstract

**Background:**

Whether acupuncture is effective for patients with functional constipation is still unclear. Therefore, we report the protocol of a randomized controlled trial of using acupuncture to treat functional constipation.

**Design:**

A randomized, controlled, four-arm design, large-scale trial is currently undergoing in China. Seven hundred participants are randomly assigned to three acupuncture treatment groups and Mosapride Citrate control group in a 1:1:1:1 ratio. Participants in acupuncture groups receive 16 sessions of acupuncture treatment, and are followed up for a period of 9 weeks after randomization. The acupuncture groups are: (1) Back-Shu and Front-Mu acupoints of Large Intestine meridians (Shu-Mu points group); (2) He-Sea and Lower He-Sea acupoints of Large Intestine meridians (He points group); (3) Combining used Back-Shu, Front-Mu, He-Sea, and Lower He-Sea acupoints of Large Intestine meridians (Shu-Mu-He points group). The control group is Mosapride Citrate group. The primary outcome is frequency of defecation per week at the fourth week after randomization. The secondary outcomes include Bristol stool scale, the extent of difficulty during defecating, MOS 36-item Short Form health survey (SF-36), Self-Rating Anxiety Scale (SAS), and Self-rating Depression Scale (SDS). The first two of second outcomes are measured 1 week before randomization and 2, 4, and 8 weeks after randomization. Other second outcomes are measured 1 week before randomization and 2 and 4 weeks after randomization, but SF-36 is measured at randomization and 4 weeks after randomization.

**Discussion:**

The result of this trial (which will be available in 2012) will confirm whether acupuncture is effective to treat functional constipation and whether traditional acupuncture theories play an important role in it.

**Trials registration:**

Clinical Trials.gov NCT01411501

## Background

Functional constipation is a common disease, both in adults and in children. The prevalence in children ranges from 0.7% to 29.6%. In adults, functional constipation affects between 0.7% and 79% of the general population [1]. The prevalence is higher in females, older individuals, those of lower socioeconomic status, and those with a lower educational level [2,3]. As a common and well-recognized public health problem, functional constipation influences patient quality of life and consumes many healthcare resources [4,5].

Several therapies (such as lifestyle changes, osmotic agents, bulking agents, and so on) [6,7] have been used in clinical practice, which is believed to be helpful in relieving symptoms. Nonetheless, many of these therapies were not proven to be effective for the condition, or were difficult to tolerate because of adverse events [8-10].

Because of the unclear etiology and pathogenesis, the therapeutic options are relatively limited. As a result, complementary or alternative therapies, such as acupuncture, are attractive to both patients and practitioners. China has a long history of managing gastrointestinal symptoms through acupuncture, including diarrhea, constipation and gastroenteritis [11]. Results of several randomized controlled trials (RCTs) showed that acupuncture may be an effective treatment for functional constipation, by improving frequency and time of defecation, and the patient’s quality of life [12-14]. However, convincing evidence for the effectiveness of treating functional constipation with acupuncture is still inadequate, due to the poor quality of current studies. Therefore, we designed a multicenter randomized controlled trial to address these problems and hopefully provide a more conclusive answer to the questions.

In this trial, we first aim at investigating whether acupuncture is effective in treating functional constipation through a comparison with Mosapride Citrate control. Second, we will attempt to determine whether different acupuncture points are the same in managing this condition. The work reported in this article is financed by the National Basic Research Program (973 Program) in China, and is registered with an identifier (NCT01411501) in Clinical Trials.gov.

## Methods and design

### Design

This is a randomized controlled, four-arm, large-scale trial comparing three acupuncture groups (using different acupuncture points) with Mosapride Citrate control group (Figures 1 and 2). Seven hundred participants will be included from the following eight hospitals: Guang’anMen Hospital of China Academy of Chinese Medical Sciences; First Affiliated Hospital of Chengdu University of Traditional Chinese Medicine (TCM); Affiliated Hospital of Anhui College of TCM; Affiliated Hospital of Changchun University of TCM; Affiliated Hospital of Guangzhou University of TCM; Affiliated Hospital of Hunan University of TCM; Affiliated Hospital of Shandong University of TCM; and Affiliated Hospital of Shanxi College of TCM. These participants will be randomly assigned to four groups (three acupuncture groups and Mosapride Citrate control group) through central randomization in a 1:1:1:1 ratio. The central randomization system will be used and performed by the Clinical Evaluation Center at the China Academy of Chinese Medical Sciences in Beijing. A random number and group assignment will be immediately received by telephone, mobile phone, or website sent from the Clinical Evaluation Center.

**Figure 1 F1:**
[figure not shown]
Trial flow chart.

**Figure 2 F2:**
[figure not shown]
**Trial processes chart.** SF-36, MOS item Short Form health survey; SAS, Self-Rating Anxiety Scale; SDS, Self-rating Depression Scale.

Participants will receive 16 sessions of acupuncture treatment over 4 weeks, with a treatment frequency of five times a week in the first 2 weeks and three times a week in the last 2 weeks. Each session will last 30 min. The follow-up period lasts 4 weeks (5 to 8 weeks after randomization). Participants will be asked to fill in constipation diaries from 1 week before randomization to 9 weeks after randomization. All outcomes are assessed at baseline and 2, 4, and 8 weeks after randomization according to the diaries.

The total research period within this study is 9 weeks for each patient. All patients are asked to record constipation diaries for 1 week before randomization (baseline phase). If they are eligible for this trial, they will be asked to finish diaries from 0 to 8 weeks after randomization.

This trial protocol has been approved by local institutional review boards and ethics committees (April 2011), and follows the principles of the Declaration of Helsinki (Version Edinburgh 2000). Before randomization all patients will be requested to sign the written informed consent, meanwhile they will be given enough time to decide whether they are willing to participate this trial, or they choose other treatment options.

### Patients

#### Study population

This study focuses on patients with functional constipation, containing a sample size of 700 participants. There are many potential factors leading to constipation, such as food, drugs, and so on. To ensure the precision of results of this trial, we developed the following eligible criteria.

#### Inclusion criteria

Participants will be included if they fulfilled the following conditions: diagnosed with functional constipation according to the criteria of the Rome III [15]; aged between 18 and 75 years old; no use of gastrointestinal drugs 1 week before randomization; provided a signed written consent form.

#### Exclusion criteria

Patients with any of the following conditions will be excluded: constipation caused by other disorders (for example, irritable bowel syndrome, post-surgery constipation, and so on); psychosis (since acupuncture is an invasive procedure and needs a treatment duration of 30 min, to ensure safety of patients with psychosis, we do not plan to include them); pregnant women or women in lactation (it is still unclear whether acupuncture will lead to abortion or other side effects); bleeding disorders (the acupuncture procedure involves penetration of the skin, therefore we will exclude participants with thrombocytopenia, and so on); serious illnesses of the heart, liver, or kidney, or other severe diseases (there may be risks that acupuncture induces stress action and thus harms patients with serious illness).

#### Recruitment procedures

Two strategies will be used to recruit participants with functional constipation. The first is to recruit participants in outpatient clinics from the eight hospitals. The chief physicians of gastroenterology and colorectal department in each hospital were invited to attend a discussion of how to recruit patients. Research assistants will be sent to their departments to help screen participants. Moreover, posters of this trial were shown outside the clinics to attract possible candidates. Second, we will post advertisements through TV broadcasts, newspapers, and so on. In these advertisements, we will briefly introduce the population we want to include, and mention the free acupuncture treatments for participants who are eligible.

### Interventions and comparison

#### Rationale for acupuncture protocol

The acupuncture protocol in this trial was formed in two steps: first, we screen for a range of acupuncture points and stimulation methods through a systematic review of records of ancient books and acupuncture textbooks, as well as results of published articles; second, meetings were held to further screen for a standardized acupuncture protocol and reach consensus among acupuncture experts in China. Based on the theory of acupuncture and TCM, Back-Shu and Front-Mu points (short for Shu-Mu points) are the classic combination for the treatment of internal organ disease, which is located in the abdomen or lower back of the body, so Back-Shu and Front-Mu acupuncture points of Large Intestine meridians are supposed to be the best points prescription to treat Large Intestine disease. Additionally, He-Sea and Lower He-Sea acupuncture points of Large Intestine meridians are also positive points prescription, which is situated in the upper or lower limbs of the body, as stated: ’He points are the best points to treat internal organ’s disease’ in *Nei Jing*. In our hypothesis, the combination of Shu-Mu points and He-sea points will achieve better therapeutic outcomes, and all the acupuncture groups will be non-inferior to Mosapride Citrate. Therefore, groups in our trial are defined as: (1) Back-Shu and Front-Mu acupoints of Large Intestine meridians (Shu-Mu points) group; (2) He-Sea and Lower He-Sea acupoints of Large Intestine meridians (He points) group; (3) Combining used Back-Shu, Front-Mu, He-Sea, and Lower He-Sea acupoints of Large Intestine meridians (Shu-Mu-He points) group; and (4) Mosapride Citrate control group (Table 1).

**Table 1 T1:** Details of acupuncture protocol

**Group names**	**Acupuncture points**	**De qi sensation**	**Stimulation**
Back-Shu and Front-Mu acupoints of Large Intestine meridians (Shu-Mu points group)	Tianshu (ST25) Dachangshu (BL25)	Yes	Both points are punctured bilaterally. Tianshu (ST25) is punctured perpendicularly 1–1.5 cun. Dachangshu (BL25) is punctured perpendicularly 0.8-1.2 cun
He-Sea and Lower He-Sea acupoints of Large Intestine meridians (He points group)	Quchi (LI11) Shangjuxu (ST37)	Yes	Both points are punctured bilaterally. Quchi (LI11) is punctured perpendicularly 0.5-1 cun. Shangjuxu (ST37) is punctured perpendicularly 1–2 cun
Combining used Back-Shu, Front-Mu, He-Sea, and Lower He-Sea acupoints of Large Intestine meridians(Shu-Mu-He points group)	Tianshu (ST25) Dachangshu (BL25) Quchi (LI11) Shangjuxu (ST37)	Yes	Stimulation is the same as above mentioned

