### Sample size calculation and statistical analysis

According to the previous literature [16], an improvement of 2.6 times (standard deviation 2.4) for defecating during 1 week with functional constipation by prucalopride is reported, and a difference of 1.6 times between groups is considered to be of clinical relevance [16]. In this study, we anticipated an improvement of 4.0 times by Shu-Mu points group, 3.8 times by He points group, 5.2 times by Shu-Mu-He points group, and 2.6 times by Mosapride Citrate tablet group. A standard deviation of 6.0 is considered, to allow a relatively high heterogeneous variance in this population. Moreover, we mainly focus on the comparison of Shu-Mu-He points group *vs*. Mosapride Citrate tablet group. So the between-group comparison will be done as: first, Shu-Mu-He points group will be compared with Mosapride Citrate tablet group as the primary comparison, since the prescription of Shu-Mu-He points is considered to be better than the other two acupuncture protocols; second, comparisons among acupuncture groups will be performed also as exploratory analysis. So, we used GPower 3.1.3 [Franz Faul, Universität Kiel, Germany], and input the four group mean defecation rates as 4.0, 3.8, 5.2, and 2.6 per week, with a common assumed standard deviation of 6.0, giving a calculated effect size of 0.15. With four groups of equal size (175/group, 700 in total) this gives the study 90% power at a 5% level of significance to detect such an overall effect size using a one-way ANOVA fixed effects omnibus test, and assuming a 15% loss to follow-up. For the pairwise comparison of primary interest (Shu-Mu-He *vs*. mosapride citrate) the study has over 90% power at a 1% level of significance (to make some adjustment for multiple comparisons) to detect a mean difference of 2.6 (5.2 to 2.6) assuming the common standard deviation of 6.0 defecations with 175 participants per group.

Statistical analysis will be performed by the Clinical Evaluation Center of China Academy of Chinese Medical Sciences in Beijing. The statistician is blinded from the allocation of groups. SPSS13.0 and SAS9.0 statistical software packages will be used to analyze the data.

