A major issue in planning the design of this trial is whether sham acupuncture should be used. Since the primary consideration of this trial is to clarify whether acupuncture is effective or whether acupuncture helps relieving symptoms of patients with functional constipation, we all agree that a pragmatic design is more suitable, which requires a positive drug as the control group. There is some evidence that Mosapride is effective for improvement of lower tract mobility, and thus is effective for management of constipation [18-20]. However, there is no proven drug clearly ahead of the rest. We choose Mosapride as a positive drug control based on: (1) it was reported to be superior to placebo for irritable bowel syndrome (IBS) patients with constipation, and it may have the potential to treat IBS patients with constipation and/or functional constipation [21]; and (2) a randomized controlled trial in China showed the same result [22], which indicates Mosapride may be a better option than other medication for Chinese population with functional constipation. So we choose Mosapride Citrate as a positive drug control. In this trial, we did not include a placebo acupuncture control, because we did not know whether acupuncture is effective for patients with functional constipation. Thus, if acupuncture is effective, then the next step would be to compare acupuncture with sham acupuncture to clarify absolute acupuncture treatment effect.

There are three different acupuncture groups in this trial, which are all expected to be effective according to traditional acupuncture theories. Combined use of Back-Shu and Front-Mu (Shu-Mu points) are regarded as the most commonly acupuncture prescription. In addition, He-Sea and Lower He-Sea points of Large Intestine meridians are also commonly used acupuncture prescription. The prescription of Shu-Mu-He points is composed of both Shu-Mu points (Shu-Mu points group, located at abdomen and lower-back) and He points (He points group, located at upper and lower limbs), which is expected to be the best therapeutic effect. Comparison of the three acupuncture groups will solve the question: whether combined use of Shu-Mu-He points will lead to better clinical outcome than using Shu-Mu or He points alone, which may give insights to whether traditional acupuncture theories work.

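### All three acupuncture groups are hypothesised to be non-inferior to mosapride, but the trial is sized and analysed only by tests of difference, with no margin or confidence-limit rule

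*Protocol article*

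**What the plan says.** Under Rationale for acupuncture protocol, the article gives a two-part hypothesis: the combined points will do better, and "all the acupuncture groups will be non-inferior to Mosapride Citrate". That covers three comparisons with mosapride.

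Under Sample size calculation and statistical analysis, the trial is sized on a different basis. The authors "input the four group mean defecation rates as 4.0, 3.8, 5.2, and 2.6 per week". Taking an SD of 6.0 in every group, they obtain an effect size of 0.15 and claim 90% power "to detect such an overall effect size using a one-way ANOVA fixed effects omnibus test". The confirmatory contrast is then named: "Shu-Mu-He points group will be compared with Mosapride Citrate tablet group as the primary comparison", with over 90% power at the 1% level for a difference of 2.6. Next in order comes: "second, comparisons among acupuncture groups will be performed also as exploratory analysis". That ordered list does not name Shu-Mu against mosapride or He against mosapride.

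The only threshold in the article is in the same section: "a difference of 1.6 times between groups is considered to be of clinical relevance". It is not called a non-inferiority margin. The listed methods are ANOVA, Kruskal-Wallis, chi-square and repeated measures, with Bonferroni adjustment. The acupuncture groups are compared with each other only after a significant difference from control.

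**The concern.** A non-inferiority hypothesis is settled by whether a confidence limit for the difference excludes a pre-stated margin. A test of equality does not answer that question. Without a margin, no result short of significant superiority can support the stated hypothesis, and no rule says what would refute it.

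The analysis sequence also sits badly with the hypothesis. An arm about equal to mosapride would be a success under the rationale, yet it gives no significant difference and so does not trigger the next step.

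At stake is the interpretation of null results for Shu-Mu and He, and of a null primary result. Background says the trial will judge whether acupuncture is effective by comparison with mosapride. A non-significant difference could then be taken as showing non-inferiority, and from there effectiveness, without evidence for either step.

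**Working it through.** **Inputs** (Sample size calculation and statistical analysis): assumed means of Shu-Mu 4.0, He 3.8, Shu-Mu-He 5.2 and mosapride 2.6, so differences from mosapride of +1.4, +1.2 and +2.6; SD 6.0; 175 per group; 15% loss, leaving 175 × 0.85 = 148.75, about 149. My assumptions: two-sided difference tests (the article does not state sidedness), one-sided 2.5% for non-inferiority, and any margin.

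**1. The plan's own figures.**
- The mean of the four means is 3.9 and the deviations are 0.1, −0.1, 1.3 and −1.3. Their SD is √(3.40/4) = 0.922, so f = 0.922/6.0 = 0.154, which agrees with the stated 0.15.
- With f = 0.1537, 90% omnibus power needs 608 evaluable participants. 608 × 1.15 = 699.2, or 700 as stated; dividing by 0.85 gives 716. Power with 595 completers is 0.895.
- Pairwise: SE = 6√(2/175) = 0.641. Power for 2.6 at 1% is Φ(2.6/0.641 − 2.576) = 0.93, so the stated figure of over 90% reproduces.

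The design is therefore sized, consistently, for tests of difference.

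**2. Power of difference tests for the other two arms**, 175 per group, Φ(d/SE − z):

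| Arm against mosapride | Two-sided 5% | Two-sided 1% |
|---|---|---|
| Shu-Mu, +1.4 | 59% | 35% |
| He, +1.2 | 46% | 24% |

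Even if the assumptions are right, the chance of a non-significant result at 5% is therefore 41% for Shu-Mu and 54% for He. With 149 per group, power at 5% falls to 52% and 41%.

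**3. What a non-significant result leaves open.** If an arm is truly worse than mosapride by 1.6, the probability of non-significance with 175 per group is Φ(1.96 − 1.6/0.641) = Φ(−0.53) = 30% at 5%, and 53% at 1%. With 149 per group it is 37% and 61%.

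Example with 148.75 per group: SE = 6√(2/148.75) = 0.696. An observed difference of −1.0 gives p = 0.15 and a 95% CI of −1.0 ± 1.96 × 0.696 = −2.36 to +0.36. The lower limit is 2.36/2.6 = 91% of the improvement assumed for mosapride.

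**4. Non-inferiority power if a margin M were set**, 149 per group, SE = 0.695, Φ((M + d)/SE − 1.96):

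| Assumed margin | d = 0 | He, d = +1.2 | Shu-Mu, d = +1.4 |
|---|---|---|---|
| 0.8 | 21% | 82% | 89% |
| 1.6 | 63% | 98% | 99% |

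Both margins are assumptions: 1.6 borrows the article's relevant difference and 0.8 is half of it. These figures are per arm, before any multiplicity adjustment.

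**The case against.** The strongest reply is that the sentence appears in a section explaining the choice of points, that the aims in Background do not mention non-inferiority, and that the named primary comparison is a coherent superiority test. Significant superiority of Shu-Mu-He would also establish non-inferiority for that arm. This stands, and it confines the problem to Shu-Mu, He and a null primary result. It does not remove the problem, because the sentence is worded as the trial's hypothesis and covers all three groups.

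A second reply is that a separate statistical analysis protocol, which the article mentions, may supply the rule. For most details that would be enough. A margin, however, determines design and size, and this article sets out its sample-size reasoning in full on another basis. The mismatch is within the text shown.

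A reader might also infer three stronger things that the documents do not support:
- *That the design could not support non-inferiority.* With a 1.6 margin and the plan's assumed benefits, power is 98 to 99% per arm.
- *That no margin could be justified because mosapride is unproven here.* Discussions does say of mosapride that "it may have the potential to treat IBS patients with constipation and/or functional constipation", but the same section cites some evidence of effectiveness in constipation and a Chinese randomised trial, and treats the drug as effective. The supportable statement is that no margin is justified in the article, which gives no effect size for mosapride itself.
- *That the investigators plan to read null results as non-inferiority.* Nothing says so. The risk is inferred: nothing in the text prevents that reading.

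**Conclusion.** The hypothesis and the analysis do not match. Non-inferiority is asserted for three arms, and the plan has no margin or decision rule that could confirm or refute it for Shu-Mu, for He, or for a non-significant Shu-Mu-He result. The primary superiority comparison is unaffected when significant (power 0.93 at 1% with 175 per group).

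The gap matters in practice because null results in the two secondary arms are likely even on the plan's own assumptions, and because a null result is weak evidence against a deficit as large as the article's own relevant difference. The size of the problem depends on the assumed SD of 6.0, two-sided tests and the stated means. The non-inferiority figures also depend on a margin that the article does not give. The favourable and unfavourable cases differ widely (98 to 99% against 63% at a margin of 1.6), which is why a rule has to be fixed in advance.

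**What to change.** Make the hypothesis and the tests agree before analysis.

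**Preferred.** Delete the non-inferiority hypothesis from Rationale for acupuncture protocol. Keep superiority of Shu-Mu-He over mosapride as the only confirmatory hypothesis. State that any non-significant acupuncture-against-mosapride result will be reported as inconclusive, with the difference and its 95% CI set against 1.6 per week, and never as non-inferior or equivalent.

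**Alternative.** If non-inferiority is kept, state and justify a margin, a confidence-limit rule and multiplicity control for the arms compared with mosapride. Trial status reports 340 participants already recruited, so this must be done without sight of comparative data.

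**Cost.** The first route changes wording only and gives up the non-inferiority claim. The second keeps the claim but needs a margin argument for which the article offers little: the 2.6 assumed for mosapride equals the improvement it reports for prucalopride, and no mosapride effect size is given.
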